## Abstract

**Background:**

Both diabetes and glucose-lowering medications have been associated with an increased risk of cancer incidence. This study will compare cancer incidence rates in individuals with and without diabetes; and will investigate, in individuals with diabetes, an association between glucose control and cancer incidence; and between the use of specific glucose-lowering medications, as well as no drug exposure, and cancer incidence.

**Methods/design:**

This is a population based historical cohort study of all individuals aged 21 years or older (about 2,300,000) who were insured by Clalit Health Services, the largest health maintenance organization in Israel during a ten-year study period. Four study groups will be established according to the status of diabetes and cancer at study entry, Jan 1, 2002: cancer free, diabetes free; cancer free, diabetes prevalent; cancer prevalent, diabetes free; and cancer prevalent, diabetes prevalent. Individuals without diabetes at study entry will be followed for diabetes incidence, and all four groups will be followed for specific cancer incidence, including second primary neoplasms. Glucose control will be assessed by HbA1c and by fasting plasma glucose levels. Time dependent regression models for cancer incidence will account for glucose-lowering medications as they are added and changed over the follow-up period. A large number of demographic and clinical variables will be considered, including: age, gender, BMI, smoking status, concomitant medications, glucose control (assessed by HbA1c and by fasting plasma glucose) and cancer screening tests.

**Discussion:**

Strengths of this study include the large population; high quality comprehensive data; comparison to individuals without diabetes, and to those with diabetes but not treated with glucose-lowering medications; and the extensive range of variables available for analysis. The great increases in diabetes prevalence and in treatment options render this study particularly relevant and timely. The Israeli national healthcare system, characterized by high standard and uniform healthcare, offers an advantageous environment for its conduct.

## Background

This study responds to a number of recent trends: the increasing prevalence of diabetes, the accumulating evidence of the relationship between diabetes and cancer
[1] and the increasing number of options available for treating diabetes. The overall aim is to elucidate the relationship between diabetes and cancer incidence (overall and specific cancers, including second primary neoplasms). Specifically, this is a ten year nationwide population-based investigation of the associations of cancer incidence with diabetes, glucose control and glucose-lowering medications.

To the best of our knowledge, a relationship between glucose control and cancer has not yet been examined. Since glucose control has been found to associate with both micro- and macrovascular complications of diabetes, and cancer is now considered a complication of diabetes, investigation of the effect of glucose control on cancer risk is relevant. Further, data on glucose control is important for the investigation of glucose-lowering medications, since initiation of treatment and switching between treatments may be related to patients’ glucose control.

The use of glucose-lowering medications has been associated with cancer incidence. Sulfonylureas and injected insulin have been found to associate positively with cancer risk
[2-5]; and metformin, which improves insulin sensitivity and lowers insulin levels, to be associated negatively with cancer risk, and to possibly have a protective role
[2-7]. A number of studies reported elevated incidence of malignancy following the use of insulin glargine
[8-10], though their methodologies have been seriously challenged
[11-14]. In particular, the Hemkens et al. study
[9] was widely criticized
[15-17] for not considering such factors as current health status, type of diabetes, intensity of glucose lowering treatment, concomitant medications, BMI, glucose control (HbA1c), hormone replacement therapy, smoking status, and cancer screening. More recently, others have tried to overcome biases by comparing glargine to human insulin, while excluding other insulin analogs
[18], or by including only individuals with type 2 diabetes
[19]. Nevertheless, those studies were criticized for short follow-up periods. Siussa et al.
[20] showed how long-term follow-up, of up to 8 years, helped distinguish between possible mechanisms for the association between glargine use and an increased risk of cancer. The proposed study, with 10 year follow-up, will assess oral glucose lowering medications, as well as insulin. We expect to reveal differential effects of glucose-lowering medications on site-specific cancer in one large population cohort.

## Methods/design

This is a large scale historical cohort study of all adult individuals insured by Clalit Health Services, the largest health maintenance organization in Israel, insuring and providing healthcare to 55% of the Israeli population (about 3.9 million people). Study entry is defined as January 1, 2002. Inclusion criteria will be: age 21 years or older at study entry and continuous insurance in Clalit Health Services from at least one year prior to study entry, January 1 2001, until the end of the study period, December 31, 2011, or until death, for those who do not survive until the end of follow-up. Of the population of over 2,300,000, over 110,000 had diabetes at study entry; and an additional 350,000 were diagnosed with diabetes during the study period (January 2002 to December 2011).

This study has three Specific Aims: First, we will compare rates of cancer incidence (overall and specific cancers, including second primary neoplasms) in individuals with and without diabetes (separately for prevalent and incident cases of diabetes). Second, we will investigate, in individuals with diabetes, the associations between measures of glucose control, as assessed by HbA1c and fasting plasma glucose, and cancer incidence (overall and specific cancers, including second primary neoplasms). Third, we will compare the incidence of cancer (overall and specific cancers, including second primary neoplasms), among individuals with diabetes who used specific glucose-lowering medications, as well as among patients with no drug exposure (periods of time during which individuals classified with diabetes did not yet purchase glucose-lowering medications, including periods on diet and exercise regimen only).

Four study groups will be established according to the status of diabetes and cancer at study entry, Jan 1, 2002 (Figure
1): cancer free, diabetes free (CF-DF); cancer free, diabetes prevalent (CF-DP); cancer prevalent, diabetes free (CP-DF); and cancer prevalent, diabetes prevalent (CP-DP). Individuals free of diabetes at study entry will be followed for diabetes incidence, and all four groups will be followed for cancer incidence (second primaries for those with prevalent cancer). Nine groups, according to diabetes and cancer prevalence at study entry, and diabetes and cancer and incidence during the study period, will be analyzed (Figure
2).

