### Data management

A database will be constructed for the proposed study from the Clalit Health Services data warehouse. Available are demographic data and vital status from the Israeli Ministry of Interior Affairs and the National Insurance Institute (Social Security); drug dispensing data from pharmacies; and medical data such as laboratory tests, imaging results, diagnoses and clinical data (blood pressure, weight, height, etc.) from Clalit Health Services in-house facilities, as well as from outside suppliers. The data are accessible at the member level, and linked to all registries, including the Cancer Registry, by means of a national identification number, a unique identifier possessed by all Israeli citizens. Data will be organized according to the BI (business intelligence) schema or infrastructure and are extracted using BI programs. Extraction is executed via the BO (business object) and SQL server management studio programs, depending on the complexity and diversity of the data requested from the data warehouse. BI analyst specialists will conduct the extraction and merge the data.

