The primary analysis will be performed using PROC PHREG of SAS version 9.2, which allows both Cox-proportional hazards models with time-dependent variables and piecewise exponential models. The piecewise exponential model divides time-at-risk into a set of pre-specified intervals with constant baseline hazard in each interval; the use of multiple intervals allows the hazard to vary with time. Clinically important time dependent covariates for the regression models include age, cholesterol (total, LDL, and HDL), concomitant medications (such as statins, beta-blockers, angiotensin converting enzyme inhibitors, and hormone replacement therapy), smoking, body mass index, blood pressure, co-morbidities (such as cardiovascular disease), and reproductive history. For each continuous variable, we will investigate appropriate transformations and interactions that might improve goodness-of-fit. The proportional hazard assumption will be evaluated using log-log survival plots, examination of Schoenfeld residuals, and testing of interactions between variables and time.

While we can not describe, or even anticipate, every contingency for this comprehensive project, we are confident that the very well qualified team has the expertise to evaluate the data.

This study was approved by the ethics committees of Sheba Medical Center, Tel Hashomer and Clalit Health Services, Israel.

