The current study will undertake various means to deal with the challenges posed by recent investigations, including comparison to a large population of individuals without diabetes in a nationwide population, and accessing a large number of potentially confounding factors and data on cancer screening.

Statistical power is expected for a number of monotherapies and combination treatments among individuals newly diagnosed with diabetes, thereby controlling for the duration of diabetes and for all glucose-lowering medications used during the course of their treatment. Temporal relationships between diabetes and cancer will be considered. A number of aspects of the study design are expected to elucidate the complex relationship between diabetes and cancer, and possible effects of glucose-lowering medications: analysis of data preceding diabetes incidence, the inclusion of “no glucose-lowering medications” as an exposure, and the inclusion of all individuals with and without diabetes who were insured by one very large health maintenance organization during a ten year period.

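### The entry rule selects the cohort on future membership: people who leave the insurer alive are dropped and all who die are kept, which biases absolute cancer rates upward

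*Protocol article*

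**What the plan says.** Methods/design fixes time zero: "Study entry is defined as January 1, 2002". The same paragraph gives two inclusion criteria, age 21 or older at entry and a membership condition. That condition starts with "continuous insurance in Clalit Health Services from at least one year prior to study entry, January 1 2001" and runs "until the end of the study period, December 31, 2011, or until death, for those who do not survive until the end of follow-up".

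Elsewhere the cohort is described as complete. Methods/design opens with "This is a large scale historical cohort study of all adult individuals insured by Clalit Health Services", and the Discussion lists among the helpful design features "the inclusion of all individuals with and without diabetes who were insured by one very large health maintenance organization during a ten year period". The membership criterion narrows both descriptions.

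The article has no rule for censoring people who leave, no count of people excluded for leaving, and no sensitivity analysis on this. The sensitivity analyses under Statistical analyses deal with other matters: reverse causation, lagged predictors, propensity scores, the prior event rate ratio and proportional hazards.

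**The concern.** The part of the criterion that looks back from entry is harmless. The part that looks forward is not, because it uses information that does not exist at time zero. Someone who leaves in 2009 is taken out of the cohort as of 2002, together with seven years of observation and any cancer diagnosed in them. Someone who dies in 2003 stays in, since death satisfies the rule.

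The two exits are treated unequally, and cancer is tied to one of them. A person who dies soon after diagnosis has little time in which to leave, whereas a survivor must avoid leaving for the full ten years. People with cancer are therefore more likely to be kept than people without it. The primary outcome is cancer incidence, and the first analyses are person-year rates for all sites and selected sites, so those rates take the bias directly. It grows with the fatality of the site, which also distorts comparisons between sites. Adjustment within the selected cohort cannot bring back the people removed.

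**Working it through.** **Plan's own figures.** None bears on this point. The article's power statement (hazard ratio 1.4, two subsets of 6000) does not depend on the criterion. The leaving rate is not given, so everything below is a range over assumed values.

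**Weight of an early death.** With a constant leaving rate *c*, a ten-year survivor is kept with probability exp(−10*c*). A person who dies at year 1 is kept with probability exp(−*c*).
- Share of ten-year survivors lost, 1 − exp(−10*c*): 4.9% at 0.5% per year, 9.5% at 1%, 18.1% at 2%.
- Over-representation of a year-1 death relative to a survivor, exp(9*c*): 1.09 at 1%, 1.20 at 2%.

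**Rate model.** Three states (cancer-free, cancer, dead) over ten years with constant hazards: cancer λ, death without cancer *d*, death after cancer *m*. Let *s* be the time left to the end of 2011.
- Probability that a person with cancer is kept: W_C(s) = [m + c·exp(−(m+c)s)] / (m+c).
- Probability that a cancer-free person is kept, W_A(s): dW_A/ds = d(1 − W_A) + λ(W_C − W_A) − c·W_A, with W_A(0) = 1.
- Observed rate divided by true rate: ∫p(t)W_C(10−t)dt / ∫p(t)W_A(10−t)dt, with p(t) = exp(−(λ+d+c)t).

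Assumed values, none from the article: λ = 0.8% per year in both groups, so the true ratio is 1; *d* = 0.8% without and 2.5% with diabetes; *m* = 15% without and 20% with diabetes.

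Example at *c* = 2%, no diabetes, ten years left: W_C = (0.15 + 0.02 × exp(−1.7)) / 0.17 = 0.904, against W_A = 0.828. The gap shrinks to nothing as *s* approaches 0; averaged over follow-up, the rate is 1.035 times the truth.

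**Equal leaving in both groups:**

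| Leaving per year | Kept, no diabetes | Kept, diabetes | Rate vs truth, no diabetes | Rate vs truth, diabetes | Diabetes ratio (true 1) |
|---|---|---|---|---|---|
| 0.5% | 0.954 | 0.957 | 1.009 | 1.009 | 1.001 |
| 1% | 0.910 | 0.917 | 1.017 | 1.019 | 1.002 |
| 2% | 0.828 | 0.841 | 1.035 | 1.039 | 1.004 |
| 5% | 0.625 | 0.653 | 1.096 | 1.105 | 1.008 |

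**Highly fatal site.** Same formulas, with *m* = 60–100% per year and an assumed site rate λ = 0.08% per year. The rate without diabetes is 1.018–1.020 times the truth at 0.5%, 1.036–1.041 at 1% and 1.075–1.086 at 2%. With equal leaving the diabetes ratio stays between 0.997 and 0.999.

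**Unequal leaving, all sites.** The table shows the diabetes ratio when the truth is 1.

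| Leaving per year, no diabetes | People with diabetes leave half as often | Same, and leaving falls to one fifth after a cancer diagnosis | Equal by diabetes, but leaving falls to one fifth after cancer |
|---|---|---|---|
| 1% | 0.992 | 0.978 | 0.999 |
| 2% | 0.984 | 0.957 | 0.998 |
| 3% | 0.976 | 0.936 | 0.997 |
| 5% | 0.958 | 0.893 | 0.995 |

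In this model, dependence of leaving on cancer alone does not move the ratio by as much as 1%. It does raise the absolute rate: without diabetes, by about 4% at 1% leaving and about 9% at 2%. It also enlarges the effect of any difference by diabetes.

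**The case against.** The strongest reply is that the aims are comparative, and with equal leaving the comparison hardly moves: less than 1% even at 5% leaving per year. Nothing in the article says that leaving differs by diabetes or treatment. The only effect size it plans for is a hazard ratio of 1.4, beside which a shift of 1–4% is modest. If leaving is rare, the absolute bias is small too. All of this stands, and it limits the size of the point. It does not remove the selection, because standardized rates are also a planned result and nothing else in the article corrects them.

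Three stronger readings are tempting and are not supported.

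- A reader might infer that the diabetes or drug hazard ratios are materially biased. A fourfold difference in leaving (0.5% against 2% per year) would shift the diabetes ratio by about 2.5% for all sites and 5–6% for highly fatal sites, but the article gives no leaving rate, let alone one by group.
- A reader might say that inclusion depends on the outcome. The rule refers to leaving and death; cancer enters only through its effect on these.
- A reader might take the statement that data are "linked to all registries, including the Cancer Registry, by means of a national identification number" to mean that cancers after leaving are captured anyway. Data management does not say that former members can be linked.

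It is also fair to object that censoring at leaving carries an assumption of its own. It is unbiased only if leaving is unrelated to cancer risk given the covariates, and the article offers no evidence on that.

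**Conclusion.** The point holds as a selection bias written into the inclusion criteria. Its certain part is the direction for absolute rates: wherever some members leave and cancer raises mortality, rates in the retained cohort are too high, and more so for fatal sites. Its size rests on the assumed leaving rate. At 0.5–2% per year, the excess is about 1–4% for all sites and about 2–9% for highly fatal sites, provided leaving does not depend on cancer.

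For the diabetes comparison, the bias is below 1% when leaving is equal by diabetes. It is roughly 1–4% when people with diabetes leave half as often, and larger if leaving also drops after a cancer diagnosis. Its direction depends on which group leaves more. The same reasoning applies to treatment groups. Whether any such difference exists cannot be judged from the article, nor from a cohort in which the leavers were never extracted. That is the main reason to change the rule before extraction.

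**What to change.** Change the inclusion criteria to age 21 or older on January 1, 2002 and continuous membership from January 1, 2001 to January 1, 2002. Follow each person to the first of the cancer outcome under analysis, death, leaving the insurer or December 31, 2011, and censor at the leaving date. No new method is needed: the planned procedure is one "which allows both Cox-proportional hazards models with time-dependent variables and piecewise exponential models", and both models accept such censoring.

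Report the number and timing of leavers by diabetes group, and show the completers-only cohort as a sensitivity analysis. The descriptions of the cohort as all insured adults should then be matched to the criterion.

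Registry follow-up after leaving is optional, and possible only if linkage is confirmed to cover former members. Drug purchases and laboratory values come from the insurer's own data warehouse, so carrying the last exposure forward after leaving would misclassify the time-dependent exposures in Aims 2 and 3.

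The cost is one changed sentence, a wider extraction and a re-count of the 2,300,000. Leavers contribute only partial follow-up, and the assumption that leaving is non-informative given covariates has to be stated.

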**Figure 1 F1:**
[figure not shown]
**The ten year follow-up of the four study groups, according to disease status at study entry: diabetes free (DF) or prevalent (DP), and cancer free (CF) or prevalent (CP).** For the groups that are DF at study entry, diabetes incidence (DI) will be followed and associated with outcomes (green arrows pointing down). For the groups that are DP at study entry, glucose control and diabetes medications will be followed and associated with the outcomes (green arrows pointing to the right). All four groups will be followed for the study outcome: overall and specific cancers, including second primary neoplasms.

**Figure 2 F2:**
[figure not shown]
**The study cohort according to diabetes and cancer status during the ten year follow-up period.** DP - prevalent diabetes; DI - incident diabetes; DF - diabetes free; CP: prevalent cancer; CI - incident cancer; CF - cancer free.

### Diabetes classification

Prevalent diabetes was determined according to physician reports to the chronic disease registry of Clalit Health Services. Incident diabetes will be determined by any one of the following criteria: two fasting glucose readings of 126 mg/dl or above during the course of a year, HbA1c greater than 7.0%, 3 recorded purchases of glucose-lowering medications during the course of a year, diagnosis of diabetes according to the Chronic Disease Registry of Clalit Health Services, or a written diagnosis by a physician (in the community or hospital). The relatively low number of individuals classified with diabetes at study entry (prevalent diabetes) is apparently due to the more limited definition of diabetes used by Clalit Health Services prior to 2002.

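### Diabetes is ascertained from the registry alone at entry but by any of five criteria afterwards, so unregistered existing cases enter the incident stratum

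*Protocol article*

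**What the plan says.** Under Diabetes classification, the protocol article gives two rules.

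- **At entry:** "Prevalent diabetes was determined according to physician reports to the chronic disease registry of Clalit Health Services". No other source is named.
- **During follow-up:** "Incident diabetes will be determined by any one of the following criteria: two fasting glucose readings of 126 mg/dl or above during the course of" (the window for the two readings is one year). The other four criteria are HbA1c above 7.0%, three drug purchases within a year, a registry diagnosis, and a physician's written diagnosis.

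The same paragraph calls the entry number relatively low and says this is "apparently due to the more limited definition of diabetes used by Clalit Health Services prior to 2002".

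The opening of Methods/design gives the counts. For entry it reads "Of the population of over 2,300,000, over 110,000 had diabetes at study entry". For follow-up it reports that "an additional 350,000 were diagnosed with diabetes during the study period". It requires membership from 1 January 2001. Nothing in the article applies the five criteria to that year or sets a washout.

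Statistical analyses splits people with diabetes into prevalent and incident for all three aims, and limits the prior event rate ratio method to incident cases. The Discussion expects adequate power "among individuals newly diagnosed with diabetes, thereby controlling for the duration of diabetes", and makes the same claim for all the glucose-lowering drugs used in the course of treatment.

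**The concern.** The case definition widens on the day follow-up starts. Anyone with diabetes who was not in the registry on 1 January 2002 starts in a diabetes-free group and moves to the incident stratum at the first qualifying result, purchase or diagnosis. The date assigned is then a date of detection, not of onset.

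Three things are at stake.

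- **Duration and drug history.** The incident stratum is meant to be the place where duration and all drugs used are known. For a missed case, duration is unknown. If that person was already treated, cumulative dose counted from the assigned date omits earlier use, and the period before that date is not free of treatment, as the prior event rate ratio method would need.
- **The prevalent and incident strata.** They differ by how cases were found as well as by when, so a difference between their hazard ratios has two possible explanations.
- **The Aim 1 comparator.** Some diabetic person-time is counted as diabetes-free until the criterion is met.

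**Working it through.** **Inputs from the article** (Methods/design; the first two are given as lower bounds): cohort N = 2,300,000; prevalent diabetes P = 110,000; incident diabetes I = 350,000 over ten years. The article gives no true entry prevalence and no estimate of the number missed, so it has no figure to reproduce.

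**Step 1: what the counts imply.**

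- Entry prevalence: 110,000 / 2,300,000 = 4.8%.
- Diabetes-free at entry: 2,300,000 − 110,000 = 2,190,000.
- Ten-year incidence: 350,000 / 2,190,000 = 16.0%, or about 16 per 1,000 per year by simple division, ignoring deaths.
- Incident to prevalent: 350,000 / 110,000 = 3.2.

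These figures are compatible with an undercount at entry. They do not measure it, because new disease and wider testing would also raise the incident count.

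**Step 2: range under an assumed true entry prevalence p.** The values of p are assumptions.

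- Missed at entry: M = p × N − P
- Share of incident cases, if all are later captured: M / I
- Implied registry sensitivity: P / (p × N)
- Share of the diabetes-free group at entry: M / 2,190,000

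| Assumed p | M | M / I | Registry sensitivity | Share of diabetes-free group |
|---|---|---|---|---|
| 5% | 5,000 | 1.4% | 96% | 0.2% |
| 6% | 28,000 | 8.0% | 80% | 1.3% |
| 7% | 51,000 | 14.6% | 68% | 2.3% |
| 8% | 74,000 | 21.1% | 60% | 3.4% |
| 10% | 120,000 | 34.3% | 48% | 5.5% |

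Each percentage point of prevalence missed is 23,000 people, or 23,000 / 350,000 = 6.6% of the incident stratum. Deaths before capture would lower every figure in the third column.

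**Step 3: person-time in the comparator.** Assume that a missed case takes one year on average to meet a criterion. Then 28,000 to 120,000 people add 28,000 to 120,000 person-years. Against roughly 2,190,000 × 10 = 21.9 million (ignoring deaths and later diabetes), that is 0.13% to 0.55%. At three years to capture it would be 0.4% to 1.6%.

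**Step 4: the rules against the claim.** The Discussion's claim needs the incident date to approximate onset and drug histories to start after it. The entry rule excludes only people in the registry, and the article itself thinks the earlier definition was too narrow. The claim does not follow for whoever that definition missed.

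**The case against.** The strongest case on the other side concerns reach and size.

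- **The scale is not shown.** The table depends wholly on the assumed prevalence, and its upper end implies that the registry held fewer than half of true cases. A reader might infer from a 16% ten-year incidence that misclassification is large. The counts cannot show that. This stands.
- **Prior treatment is not shown.** A reader might infer that the missed cases were long-standing and already on drugs. The article says only that the earlier definition was narrower, and hedges even that. If it mainly missed mild or untreated disease, the harm to drug histories shrinks, though duration remains unknown. This stands.
- **The comparator is barely affected.** A regularly treated person leaves the diabetes-free group at the third purchase. Step 3 supports this, although untreated and untested people could stay longer.
- **Not everything rests on the incident stratum.** All three aims are also run in prevalent cases, and the prior event rate ratio work is exploratory. The registry is one of the five incident criteria, so the strata are not purely two definitions. This stands too.
- **The undercount is disclosed, and this is a condensed article.** A full protocol may hold a look-back rule. But the article states both definitions, reports counts under them, remarks on the low entry number and continues. Its general sensitivity analyses, and its plan to analyse data from before diabetes incidence, are not tied to this problem. The point concerns a rule as stated, not a detail left out.

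**Conclusion.** The point holds for the asymmetry and its effect on the incident stratum. As the rules stand, existing but unregistered cases are counted first as diabetes-free and then as incident. The claim to control for duration and for all drugs used is therefore not secured, and the prevalent and incident strata differ by definition as well as by timing.

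The size is unknown: 8% to 34% of incident cases for an assumed true entry prevalence of 6% to 10% with full later capture, and little if true prevalence was close to the recorded 4.8%. The effect on the diabetes-free comparator is probably small. The article does not support saying that a large share of incident cases is known to be misclassified, that those cases were previously treated, or that Aim 1 is seriously biased by this route.

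The rule should still be corrected before hazard ratios are seen, because group assignment underlies every analysis and a later change would be post hoc.

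**What to change.** 1. Apply the same five criteria, unchanged, to calendar 2001 and class anyone positive as prevalent. Membership in that year is already required, and this uses only information from before entry. Do not loosen the pharmacy criterion to any single purchase, which would create a new asymmetry.
2. If 2001 laboratory or pharmacy data are incomplete (the article guarantees membership, not data), use 2002 as a washout year. Class those who qualify in it as prevalent, and start at-risk time for all groups on 1 January 2003.
3. Add a sensitivity analysis that excludes cases first qualifying in the first one to two years of follow-up from the duration, cumulative-dose and prior event rate ratio analyses. One year of look-back will not find people who were untested in it.
4. Requiring an earlier non-diabetic test should be a sensitivity analysis only, because it selects on testing in a study concerned with surveillance bias.
5. Soften the Discussion's duration claim to match what the look-back can support.

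**Cost:** one more year of data passed through the same criteria, and a smaller incident stratum. The washout also costs one of the ten years of follow-up. At the average of 350,000 / 10 = 35,000 cases a year, it would move about 10% of incident cases to prevalent, some of them truly new in 2002.
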